## Appendices

### Appendix A

#### International Physical Activity Questionnaire (IPA-Q)

Participant ID: \_\_\_\_\_ Gender: ☐ Male ☐ Female

Age: : \_\_\_\_\_

We are interested in finding out about the kinds of physical activities that people do as part of their everyday lives. The questions will ask you about the time you spent being physically active in the last 7 days. Please answer each question even if you do not consider yourself to be an active person. Please think about the activities you do at work, as part of your house and yard work, to get from place to place, and in your spare time for recreation, exercise or sport.

Think about all the vigorous activities that you did in the last 7 days. Vigorous physical activities refer to activities that take hard physical effort and make you breathe much harder than normal. Think only about those physical activities that you did for at least 10 minutes at a time.

1. During the last 7 days, on how many days did you do vigorous physical activities like heavy lifting, digging, aerobics, or fast bicycling?

A. Yes, \_\_\_\_\_ days per week

B. No vigorous physical activities Skip to question 3

2. How much time did you usually spend doing vigorous physical activities on one of those days? \_\_\_\_\_ hours per day

Think about all the moderate activities that you did in the last 7 days. Moderate activities refer to activities that take moderate physical effort and make you breathe somewhat harder than normal. Think only about those physical activities that you did

for at least 10 minutes at a time.

3. During the last 7 days, on how many days did you do moderate physical activities like carrying light loads, bicycling at a regular pace, or doubles tennis? Do not include walking.

A. Yes, \_\_\_\_\_ days per week

B. No moderate physical activities Skip to question 5

4. How much time did you usually spend doing moderate physical activities on one of those days? \_\_\_\_\_ hours per day

Think about the time you spent walking in the last 7 days. This includes at work and at home, walking to travel from place to place, and any other walking that you might do solely for recreation, sport, exercise, or leisure.

5. During the last 7 days, on how many days did you walk for at least 10 minutes at a time?

A. Yes, \_\_\_\_\_ days per week

B. No walking Skip to question 7

6. How much time did you usually spend walking on one of those days?  
\_\_\_\_\_ hours per day

The last question is about the time you spent sitting on weekdays during the last 7 days. Include time spent at work, at home, while doing course work and during leisure time. This may include time spent sitting at a desk, visiting friends, reading, or sitting or lying down to watch television.

7. During the last 7 days, how much time did you spend sitting on a week day?  
Yes, \_\_\_\_\_ minutes per day

This is the end of the questionnaire, thank you for participating.

## Appendix A (Chinese Version)

### 国际体力活动问卷 (IPAQ)

编号: \_\_\_\_\_ 性别: ☐ 男 ☐ 女

年龄: \_\_\_\_\_ 岁

目的: 了解人们在日常生活中所做的各种体育活动。这些问题会问你在过去 7 天里做了多少运动。请回答每一个问题, 即使你不认为自己是一个积极的人。请想想你在工作中做的活动, 作为你的房子和院子工作的一部分, 从一个地方到另一个地方, 以及在你的空闲时间娱乐, 锻炼或运动。

1. 过去 7 天中你是否进行过剧烈的体力活动, 如搬举重物、上楼梯、爬山、用锄头锄土、搬堆家具、快速骑自行车、剧烈体育锻炼 (跑步、跳绳、健身房内健身操等) 且持续时间超过 10 分钟?

是, 天数为 \_\_\_\_\_ 否, 跳到问题 3

2. 在这几天中, 你每天进行这些剧烈体力活动的时间是多少? \_\_\_\_\_ 分钟/天

3. 在过去 7 天中, 你是否进行过中等强度体力活动, 如搬举轻物、整理庭院/阳台、用手擦地、用手洗衣服、清洗门窗用大剪刀修剪花草、铺床、下楼梯、打羽毛球、乒乓球、一般速度骑自行车 (当作交通工具)、做瑜伽、练太极拳等且每次活动持续时间超过 10 分钟?

是, 天数为 \_\_\_\_\_ 否, 跳到问题 5

4. 在这几天中, 你每天进行这些中等强度体力活动的时间是多少? \_\_\_\_\_ 分钟/天

5. 在过去的 7 天中你是否有每次至少 10 分钟的步行? 包括您工作时、在家中的步行、交通行程的步行以及为了锻炼身体进行的步行。

是, 天数为 \_\_\_\_\_ 否, 跳到问题 7

6. 在这几天中, 你每天步行的时间是多少? \_\_\_\_\_ 分钟/天

7. 在过去的 7 天中, 你通常每天处于久坐的身体状态有多长时间? 包括在家、工作场所及闲暇时间里, 可能出现在拜访亲友、看书读报、坐着或躺卧看电视以及坐在电脑前 (不包括睡眠时间)。 \_\_\_\_\_ 分钟/天

## Appendix B

### Physical Activity Readiness Questionnaire (PAR-Q)

Participant ID: \_\_\_\_\_ Gender: ☐ Male ☐ Female

Age: : \_\_\_\_\_

Purpose: This stage is mainly used for self-assessment. Identify the subjects' known ailments or symptoms of diseases that may be at high risk during tai chi exercise.

| Topic                                                                                                                                                              | Please tick(✓) |    |
|--------------------------------------------------------------------------------------------------------------------------------------------------------------------|----------------|----|
| 1.Has your doctor ever told you that you have a heart attack or that you've had a stroke?                                                                          | Yes            | No |
| 2. Have you ever experienced excruciating pain in your chest while resting or while exercising?                                                                    | Yes            | No |
| 3. Have you ever lost your balance due to dizziness or fainting while exercising?                                                                                  | Yes            | No |
| 4. Have you had an asthma attack in the past 12 months that required immediate medical attention?                                                                  | Yes            | No |
| 5. Have you ever had a diagnosed muscle, bone, joint or neurological problem that you were told might get worse as a result of participating in physical exercise? | Yes            | No |
| 6. Do you know that you have other problems that make you unfit for sports?                                                                                        | Yes            | No |
| 7. Have you practiced Tai Chi or participated in any meditation exercise in the past 3 months?                                                                     | Yes            | No |

If you answered "yes" to any of the 7 questions, please seek guidance from your family doctor or appropriate allied health professional before engaging in physical activity. If you answered "no" to all of the seven questions, and you have no other health concerns, then you can do light moderate physical activity exercise.

I believe, to the best of my knowledge, that all the information I have provided in this tool is correct.

## Appendix B (Chinese Version)

### 身体状况问卷 (PARQ)

编号: \_\_\_\_\_ 性别: ☐ 男 ☐ 女

年龄: \_\_\_\_\_ 岁

目的: 这个阶段主要用于自我评估。确认受试者的已知疾病或者疾病的症状, 在太极运动的过程中, 这些疾病可能具有很高的风险性。我相信, 据我所知, 我在这个工具中提供的所有信息都是正确的。

| 题目                                                 | 打勾 (✓) |   |
|----------------------------------------------------|--------|---|
| 1. 你的医生是否曾经告诉过你有心脏病或者你曾经是否遭受过中风?                   | 是      | 否 |
| 2. 当你在体息的时候或者运动的过程中, 你的胸部是否经历过难以忍受的疼痛?             | 是      | 否 |
| 3. 当你运动的过程中, 你是否有过头晕或者昏厥导致你失去平衡?                   | 是      | 否 |
| 4. 在过去的 12 个月中, 你是否有哮喘发作需要立即的医疗治疗?                 | 是      | 否 |
| 5. 你有没有被诊断过的肌肉、骨骼关节或神经类问题, 你被告知可能是否会因为参加体育锻炼而变得更糟? | 是      | 否 |
| 6. 你是否知道自己还有其他的问题, 导致不适合参加运动?                      | 是      | 否 |
| 7. 你有没有习练过太极, 在过去 3 个月内是否参加过冥想类运动?                 | 是      | 否 |

如果您对 7 个问题中的任何一个都回答“是”, 请在进行体力活动之前向您的家庭医生或适当的专职保健专业人员寻求指导。

如果你对 7 个问题中的所有问题都回答“不”, 并且你对健康没有其他的担心, 那么你可以进行轻度中等强度的体力活动锻炼。

## Appendix C

### Depression Status Inventory

Participant ID: \_\_\_\_\_ Gender: ☐ Male ☐ Female

Age: : \_\_\_\_\_

For each statement below, please circle the number in the column that best represents how you have been feeling or behaving in the last several days.

| Topic                                          | A little of
the time | Some of
the time | A Good
part of
the time | Most of
the time |
|------------------------------------------------|-------------------------|---------------------|-------------------------------|---------------------|
|                                                | Please tick(✓)          |                     |                               |                     |
| 1. I feel down-hearted and blue.               | 1                       | 2                   | 3                             | 4                   |
| 2. Morning is when I feel the best.            | 4                       | 3                   | 2                             | 1                   |
| 3. I have crying spells or feel like it.       | 1                       | 2                   | 3                             | 4                   |
| 4. I have trouble sleeping at night            | 1                       | 2                   | 3                             | 4                   |
| 5. I eat as much as I used to.                 | 4                       | 3                   | 2                             | 1                   |
| 6. I still enjoy sex.                          | 4                       | 3                   | 2                             | 1                   |
| 7. I notice that I am losing weight.           | 1                       | 2                   | 3                             | 4                   |
| 8. I have trouble with constipation.           | 1                       | 2                   | 3                             | 4                   |
| 9. My heart beats faster than usual.           | 1                       | 2                   | 3                             | 4                   |
| 10. I get tired for no reason.                 | 1                       | 2                   | 3                             | 4                   |
| 11. My mind is as clear as it used to be.      | 4                       | 3                   | 2                             | 1                   |
| 12. I find it easy to do the things I used to. | 4                       | 3                   | 2                             | 1                   |
| 13. I am restless and can't keep still.        | 1                       | 2                   | 3                             | 4                   |

|                                                            |   |   |   |   |
|------------------------------------------------------------|---|---|---|---|
| 14. I feel hopeful about the future.                       | 4 | 3 | 2 | 1 |
| 15. I am more irritable than usual.                        | 1 | 2 | 3 | 4 |
| 16. I find it easy to make decisions.                      | 4 | 3 | 2 | 1 |
| 17. I feel that I am useful and needed.                    | 4 | 3 | 2 | 1 |
| 18. My life is pretty full.                                | 4 | 3 | 2 | 1 |
| 19. I feel that others would be better off if I were dead. | 1 | 2 | 3 | 4 |
| 20. I still enjoy the things I used to do.                 | 4 | 3 | 2 | 1 |

Add up all of the numbers that were circled and consult the scale provided below:

The scores range from 25-100. TM

25-49 Normal Range TM

50-59 Mildly Depressed TM

60-69 Moderately Depressed TM

70 and above Severely Depressed

## Appendix C (Chinese Version)

### 抑郁状态问卷(DSI)

编号: \_\_\_\_\_ 性别: ☐ 男 ☐ 女

年龄: \_\_\_\_\_岁

指导语: DSI 由 20 个陈述句和相应问题条目的组成, 请被测试者根据最近一周的情况, 对每一个条目均按 1、2、3、4 四级给予评分, 请如实回答以下 20 项症状。

| 题目                                       | 偶尔或无  | 有时 | 经常 | 持续 |
|------------------------------------------|-------|----|----|----|
|                                          | 打勾(√) |    |    |    |
| 1. 你感到情绪沮丧, 郁闷吗?                         | 1     | 2  | 3  | 4  |
| 2. 你要哭或想哭吗?                              | 4     | 3  | 2  | 1  |
| 3. 你感到早晨心情最好吗?                           | 1     | 2  | 3  | 4  |
| 4. 你夜间睡眠不好吗?经常早醒吗?                       | 1     | 2  | 3  | 4  |
| 5. 你吃饭象平时一样多吗?食欲如何?                      | 4     | 3  | 2  | 1  |
| 6. 你感到体重减轻了吗?                            | 4     | 3  | 2  | 1  |
| 7. 你的性功能正常吗?乐意注意具有吸引力的异性, 并好和他/她在一起、说话吗? | 1     | 2  | 3  | 4  |
| 8. 你为便秘烦恼吗?                              | 1     | 2  | 3  | 4  |
| 9. 你的心跳比平时快吗?                            | 1     | 2  | 3  | 4  |
| 10. 你无故感到疲劳吗?                            | 1     | 2  | 3  | 4  |
| 11. 你坐卧不安, 难以保持平静吗?                      | 4     | 3  | 2  | 1  |
| 12. 你做事情比平时慢吗?                           | 4     | 3  | 2  | 1  |
| 13. 你的头脑象往常一样清楚吗?                        | 1     | 2  | 3  | 4  |

|                        |   |   |   |   |
|------------------------|---|---|---|---|
| 14. 你感到生活很空虚吗?         | 4 | 3 | 2 | 1 |
| 15. 你对未来感到有希望吗?        | 1 | 2 | 3 | 4 |
| 16. 你觉得决定什么事很容易吗?      | 4 | 3 | 2 | 1 |
| 17. 你比平时更容易激怒吗?        | 4 | 3 | 2 | 1 |
| 18. 你仍旧喜爱自己平时喜爱的事情吗?   | 4 | 3 | 2 | 1 |
| 19. 你感到自己是有用的和不可缺少的人吗? | 1 | 2 | 3 | 4 |
| 20. 你曾经想过自杀吗?          | 4 | 3 | 2 | 1 |

注:1972年 Zung 氏增编了与自评抑郁量表(Self-Rating Depression Scale, SDS)相应的检查者用本,改自评为他评,称为抑郁状态问卷(Depression Status Inventory, DSI)。评定时间跨度为最近一周。DSI 由 20 个陈述句和相应问题条目的组成。每一条目相当于一个有关症状,按 1-4 级评分。

评分方法:每一个条目均按 1、2、3、4 四级评分。20 个条目中有 10 项(第 2、5、6、11、12、14、16、17、18 和 20)是用正性词陈述的,为反序计分,其余 10 项是用负性词陈述的,按上述 1-4 顺序评分。

条目反映抑郁状态四组特异性症状:

1. 精神性——情感症状,包含抑郁心境和哭泣两个条目;
2. 躯体性障碍:包含情绪的日间差异、睡眠障碍、食欲减退、性欲减退、体重减轻、便秘、心动过速、易疲劳共八个条目;
3. 精神运动性障碍,包含精神运动性迟滞和激越两个条目;
4. 抑郁的心理障碍,包含思维混乱、无望感、易激惹、犹豫不决、自我贬值、空虚感、反复思考自杀和不满足,共八个条目。

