## **3.4 Experimental apparatus, procedure, and measure assessment**

### **3.4.1 Depression Status Inventory**

The state of depression can be measured by Depression Status Inventory (DSI; Zung 1965), DSI consists of 20 items, and each item has four answers, in which it is assigned 1 to 4 points according to the time level. Total scores of all items range from 20 to 80, and lower scores represent a "lower state of depression" (Kim et al., 2004). Compared to the clinical judgment of a psychiatrist, the reliability of the DSI was 0.90, the specificity of the DSI was 0.80, and the sensitivity of the DSI was 0.90 (Alber et al., 1992).

DSI is a short-term evaluation scale and questionnaire for others. It is convenient to operate and easy to grasp. It can effectively reflect the symptoms of  
Version number2.0 ; Dated 15thFeb. 2022

depression and their severity and changes. It is especially suitable for general hospitals to find depression patients. If the subject has a low level of education or intelligence and cannot perform self-assessment, DIS can be used to evaluate the examiner. DIS has been widely used abroad. Mainland of China was translated into Chinese in 1985 and was first used to evaluate the efficacy of the antidepressant minaprine in the treatment of depression and clinical research on depression.

Scoring method: Each item is scored on four levels of 1, 2, 3, and 4. There are a total of 20 items, which reflect the four groups of specific symptoms of depression: Psychic-emotional symptoms, including two items of depression and crying; Physical disorders: eight items including day-to-day differences in mood, sleep disorders, constipation, appetite loss, libido loss, fatigue, weight loss and tachycardia; Psychomotor disorder, including psychomotor retardation and agitation; Psychological disorders of depression, including confusion, hopelessness, irritability, indecision, self-devaluation, feeling of emptiness, suicidal thinking and dissatisfaction, a total of eight items. In these 20 items, 10 items are set in positive words, which are scored in reverse order, and the remaining 10 items are negative words that should be scored in the order of 1-4 above. The scores range from 25 to 100, normal scores range from 25 to 49, Mildly Depressed scores range from 50 to 59, Moderately Depressed scores range from 60 to 69, and Severely Depressed scores are 70 and above.

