all, 2 means some, 3 means moderate, and 4 means very obvious. In T-AI, 1 means almost none, 2 means some, 3 means often, 4 means almost always. The subjects choose the most suitable score based on their own experience. All positive emotion items are scored in reverse order. Calculate the cumulative scores of the S-AI and T-AI scales, with a minimum of 20 and a maximum of 80, reflecting the degree of state or trait anxiety (Hui, 2020).

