### STAI Form Y-2

**DIRECTIONS:** A number of statements which people have used to describe themselves are given below. Read each statement and then circle the appropriate number to the right of the statement to indicate how you generally feel. There are no right or wrong answers. Do not spend too much time on any one statement but give the answer which seems to describe how you generally feel.

| Topic                                    | Not at
all  | Somew
hat | Moderat
ely so | Very
much
so |
|------------------------------------------|----------------|--------------|-------------------|--------------------|
|                                          | Please tick(✓) |              |                   |                    |
| 21. I feel pleasant.                     | 1              | 2            | 3                 | 4                  |
| 22. I feel nervous and restless.         | 1              | 2            | 3                 | 4                  |
| 23. I feel satisfied with myself.        | 4              | 3            | 2                 | 1                  |
| 24. I wish I could be as happy as others | 4              | 3            | 2                 | 1                  |

|                                                                                              |   |   |   |   |
|----------------------------------------------------------------------------------------------|---|---|---|---|
| seem to be.                                                                                  |   |   |   |   |
| 25. I feel like a failure.                                                                   | 1 | 2 | 3 | 4 |
| 26. I feel rested.                                                                           | 4 | 3 | 2 | 1 |
| 27. I am “calm, cool, and collected”                                                         | 4 | 3 | 2 | 1 |
| 28. I feel that difficulties are piling up so that I cannot overcome them.                   | 1 | 2 | 3 | 4 |
| 29. I worry too much over something that really doesn't matter.                              | 1 | 2 | 3 | 4 |
| 30. I am happy .                                                                             | 4 | 3 | 2 | 1 |
| 30. I have disturbing thoughts.                                                              | 1 | 2 | 3 | 4 |
| 31. I lack self-confidence.                                                                  | 1 | 2 | 3 | 4 |

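### The Chinese DSI form carries the reverse-scoring key of the English item order, so 12 of its 20 items are scored in the wrong direction and the depression total is nearly uninformative and, on balance, reversed

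*Protocol*

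**What the plan says.** **DSI, rule in the body.** Protocol section 3.4.1 describes 20 items scored 1 to 4 and says that "10 items are set in positive words, which are scored in reverse order"; the other ten are scored in direct order. It states "Total scores of all items range from 20 to 80", with lower meaning less depressed. The same section then gives a range of 25 to 100 with bands at 50, 60 and 70.

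**DSI, English form (Appendix C).** Items 2, 5, 6, 11, 12, 14, 16, 17, 18 and 20 are printed 4-3-2-1. All ten are positively worded; item 2, for example, is "2. Morning is when I feel the best". The form then instructs: "Add up all of the numbers that were circled and consult the scale provided below". The scale below that instruction is the 25 to 100 one.

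**DSI, Chinese form (Appendix C, Chinese version).** The table prints 4-3-2-1 for the same ten item numbers, and the note repeats them: "20 个条目中有 10 项(第 2、5、6、11、12、14、16、17、18 和 20)是用正性词陈述的". This form prints no cut-offs.

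**STAI.** Section 3.4.2 says "All positive emotion items are scored in reverse order". It gives the state scale as half positive and half negative, and the trait scale as 9 positive and 11 negative items. Both language versions in Appendix D print items 1 and 21 as 1-2-3-4 and item 24 as 4-3-2-1.

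**Use.** Section 3.6 lists depression and anxiety as tertiary outcomes, analysed by a two-way repeated-measures ANOVA.

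**The concern.** A reverse-scoring list belongs to one particular item order. The Chinese form has its own order but carries the English list. Chinese item 2 asks about crying and is reversed, while "15. 你对未来感到有希望吗" (hope for the future) is not. The note on the Chinese form also names crying, weight loss, agitation, slowing, irritability, emptiness and suicidal thinking as depressive symptoms, yet the key gives each of them its lowest code when the symptom is constant.

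The trial recruits at a Chinese university and appends Chinese forms, so these are very likely the ones in use, although the protocol does not say so outright. Scored as printed, the total would not measure what section 3.4.1 says it measures, and the depression comparison would be invalid. Because the protocol fixes this key itself, it is not a detail left to an analysis plan.

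**Working it through.** **1. Key against wording, Chinese DSI.** Inputs: the item wording and printed codes in Appendix C (Chinese version), and the rule in 3.4.1 that only positive items are reversed.

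| Items | Wording | Printed | Result |
|---|---|---|---|
| 1, 4, 8, 9, 10 | symptom | 1-2-3-4 | right |
| 5, 16, 18 | positive | 4-3-2-1 | right |
| 2, 6, 11, 12, 14, 17, 20 (crying, weight loss, restless, slower, empty, irritable, suicidal thoughts) | symptom | 4-3-2-1 | wrong |
| 3, 7, 13, 15, 19 (best in the morning, normal sexual function, clear mind, hopeful, useful) | positive | 1-2-3-4 | wrong |

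Right: 5 + 3 = 8. Wrong: 7 + 5 = 12.

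**2. Where the list comes from.** On the English form all ten listed items are positive, so the key is right there. In Chinese, eight of those contents are still positive and now stand at 3, 5, 7, 13, 15, 16, 18 and 19. The other two (ease of doing things, full life) have become symptom items 12 and 14. The Chinese form therefore has 8 positive items, not the 10 stated.

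**3. Totals at the extremes with the printed key.**
- No symptoms: 8×1 + 12×4 = 56.
- Every symptom at its maximum: 8×4 + 12×1 = 44.
- Correct key: 20×1 = 20 and 20×4 = 80.
- Net factor for a uniform change: (8 − 12)/20 = −0.2. The same figure follows from (44 − 56)/(80 − 20). A uniform fall of 5 points would show as a rise of 1.

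**4. Correlation of the printed with the correct total.** Assume that the correctly scored items have equal variance and a common correlation r. The documents give no r, so a range is shown.
- Covariance: −4(1 + 19r). Variance of the correct total: 20(1 + 19r). Variance of the printed total: 20 − 4r.
- Correlation = −4√(1 + 19r) / √[20(20 − 4r)].

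| r | 0.1 | 0.2 | 0.3 | 0.4 |
|---|---|---|---|---|
| correlation | −0.34 | −0.45 | −0.53 | −0.61 |

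**5. What a real effect would look like.** Take an assumed uniform fall of 0.4 SD on the correct total. In SD units the printed score shows it multiplied by the correlation above: a rise of 0.4×0.344 = 0.14 SD to 0.4×0.611 = 0.24 SD. With 25 per group (section 3.2.2), a simple two-group comparison has standardised shift d×√(25/2) = 0.49 to 0.86. The chance of significance in the wrong direction is P(Z > 1.96 − shift), about 7% to 14%. This is a rough normal approximation, not the planned ANOVA.

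**6. STAI.** The state scale has ten positive items, of which nine are reversed; item 1 is missed. On the trait scale the nine positive items are complete without item 24 ("24. I wish I could be as happy as others" and its continuation), so on the protocol's own 9/11 split item 24 is negative. It is reversed all the same, while positive item 21 is not.
- State range: 19×1 + 1×4 = 23 to 19×4 + 1×1 = 77.
- Trait range: 18×1 + 2×4 = 26 to 18×4 + 2×1 = 74.
- Both should run from 20 to 80. They are compressed, not reversed.

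**7. DSI scale.** 20×1.25 = 25 and 80×1.25 = 100, so the second range is consistent with an unstated factor of 1.25. The band limits 50, 60 and 70 then equal raw sums of 40, 48 and 56. Read as the English form instructs, raw sums of 40 to 49 (50 to 61.25 converted) would be classed as normal.

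**The case against.** The strongest reply concerns reach, and most of it stands. Depression and anxiety are tertiary in section 3.6, and the Stroop, HRV and EEG outcomes and the sample size do not depend on them. Respondents tick one column per item, so retained item responses can be re-scored by wording even after collection. The body rules on reversal are right in principle; it is the appendix keys that break them.

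Three stronger readings are tempting and are not supported:

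- **That the trial would reach the opposite conclusion on depression.** The reversal is a net effect of −0.2. Under the assumptions in the working, a significant result in the wrong direction has a chance of only about 7% to 14%. A missed effect is likelier, and an uneven change across symptoms could move the total either way.
- **That severity classes would be inverted.** Totals of 56 and 44 do fall in the mild and normal bands, but those bands, and the instruction to add up and consult them, are on the English form; section 3.4.1 repeats the bands. The Chinese form has neither, and the planned ANOVA uses no severity class.
- **That the DSI cut-offs are themselves wrong.** The documents show only that the summed score and the bands are on different scales. Multiplying by 1.25 is linear and leaves every F and p value unchanged.

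A transcription artefact can be ruled out for the DSI key, because the table and the note print the same ten numbers.

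**Conclusion.** The Chinese DSI key is wrong as written. The count of 12 mis-keyed items out of 20 is exact and rests only on item wording and printed codes. The 56 to 44 span and the factor −0.2 assume that all symptoms move together; the correlations of −0.34 to −0.61 also assume equal item variances and a common inter-item correlation of 0.1 to 0.4. A score produced by following this form is nearly uninformative and on balance reversed, so a real benefit would probably be missed or appear as a small worsening. This invalidates one tertiary outcome as scored and leaves the primary outcomes alone. It also presumes that the Chinese form is the one used, which is very likely but not stated.

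The STAI fault is real and much smaller: 3 of 40 items, with attenuation and no reversal. The two DSI scales are a contradiction that bears on classification only.

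**What to change.** 1. On the Chinese DSI, reverse-score only items 3, 5, 7, 13, 15, 16, 18 and 19. Correct both the table and the note.
2. In section 3.4.1, amend the statement of ten positive and ten negative items so that it is right for the Chinese form (8 and 12).
3. Record item-level responses and score them from one checked script. If forms have already been completed, re-score them by wording.
4. In both STAI versions, reverse items 1 and 21 and un-reverse item 24.
5. State one DSI scale in section 3.4.1 and on the English form before any severity class is reported: either the raw sum of 20 to 80, or the raw sum × 1.25 with the 25 to 100 bands.

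The cost is an edit to two appendices and one section, plus a short scoring script and its check. Sample size, visits and the planned ANOVA do not change. If only totals have been stored, the item responses must be re-entered from the forms.
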